# A randomised crossover trial of staff time with proned patients in the ICU using the ‘BathMat’

**DOI:** 10.1186/s13063-025-09221-x

**Published:** 2025-11-13

## Abstract

**Background:**

The technique of turning a ventilated patient into the prone position is one which has a strong evidence base for improving both oxygenation and patient survival in the intensive care unit (ICU). As such, proning is advocated in national and international guidance. To mitigate the risk of complications, national guidance recommends repositioning proned patients every 2–4 h. The current process of repositioning is associated with risk and requires multiple staff members recurrently during the period of prone therapy. There is therefore an urgent need to explore safer and more efficient techniques. To address these issues, a multi-vessel inflatable pillow (the ‘BathMat’) has been developed which aims to improve the safety and ease of repositioning, whilst reducing the number of staff and the time required. Inflation of the BathMat, which is placed beneath a proned patient, allows easy repositioning of the head and arms, before deflation returning the patient to the resting position. The device requires clinical testing to assess its benefits outside of simulated scenarios.

**Methods:**

The BathMat trial is a randomised, multicentre, single-blind crossover study of repositioning in ventilated proned patients in ICU using the BathMat vs conventional care. Ventilated patients who require proning will be randomised to be repositioned with standard care or the BathMat. The same repositioning method will be used throughout each proning session, but will alternate on subsequent proning sessions between BathMat and standard care. The primary outcome is the difference in total staff time (number of staff × total time taken) required to reposition a patient with the BathMat compared with standard care. Secondary outcomes are the number of repositioning exercises performed, the number of adverse incidents associated with repositioning, the ease of manual handling, and the health economic costs of the complications of proning.

**Discussion:**

This is the first clinical trial of a device specifically designed to improve the quality of patient care delivered and improve the staffing resources required to care for proned ICU patients. The impact potential for patients and staff is significant, through liberation of staff, improved manual handling, and risk mitigation for proned patients.

Trial registration

ClinicalTrials.gov NCT06844617. Registered on Jan. 19, 2025. https://clinicaltrials.gov/study/NCT06844617

**Supplementary Information:**

The online version contains supplementary material available at 10.1186/s13063-025-09221-x.

## Administrative information

Note: the numbers in curly brackets in this protocol refer to SPIRIT checklist item numbers. The order of the items has been modified to group similar items (see http://www.equator-network.org/reporting-guidelines/spirit-2013-statement-defining-standard-protocol-items-for-clinical-trials/).

## Background and rationale

Approximately 235,000 patients per year are admitted to ICU in the UK. One of the most common reasons to be admitted to an ICU is the need for respiratory support. Evidence suggests that over 16,500 ICU patients per year (7%) [1] have lung injury of significant severity that proning will be beneficial to improve both oxygenation and chances of survival. Proning describes the technique whereby sedated patients on a ventilator are turned onto their front. Once proned, patients stay on their front for 16–18 h. Depending upon the patient’s condition, this process may be repeated up to five times during an ICU stay, although during the COVID-19 pandemic, some patients were proned up to 10 times. The use of proning has been shown to reduce the risk of death by 17.4% [2]; this is one of the greatest reductions in mortality from a single intervention in intensive care medicine, and this underpins the enthusiasm of clinicians to employ the technique. Whilst proned, a patient’s head needs to be turned and their arms repositioned (hereafter termed ‘repositioning’) regularly to minimise the risk of pressure sores and nerve/organ injuries. This task requires a team of five or more staff and takes 30–60 min to perform (more if full personal protective equipment (PPE) is required).

The evidence that proning improves oxygen levels and survival rates in patients who are severely oxygen dependent in ICU is irrefutable. As such, the technique forms an essential component of national and international guidance for ICU clinicians. Complications associated with proning are well described [3]. To mitigate the risk of complications, national guidance recommends repositioning every 2–4 h. Greater awareness of the benefits of proning following the COVID-19 pandemic means that the use of the technique may be more readily employed in the post-pandemic era. This increase, in combination with the unwieldy, demanding, and far from risk-free repositioning process (described below), means there is an urgent need to explore safer and more efficient repositioning techniques.

Repositioning is currently typically carried out in one of four ways:The patient is slid up the bed to allow their supported head (now clear of the mattress) to be rotated before returning to the original position. This is the most common method in the UK [4] and is recommended in national and international guidance. It requires at least 5 staff and is associated with a significant manual handling exercise.A hoist can be used to lift the patient off the bed to allow repositioning whilst elevated. Hoists are large devices that require 3–5 staff to operate, they can be difficult to manoeuvre and are typically limited in number on an ICU. This approach requires the insertion/removal of slings, takes approximately the same amount of time as a manual turn described above, and can lead to unpredictable movement of the patient whilst suspended.A specialist proning bed can be used. This is prohibitively expensive (£800+ per day), complicated, and requires large areas for storage when not in use. This approach requires a specialist bed per patient, thereby limiting the number of patients that can be simultaneously proned on any given ICU. This approach is the least preferred and least used repositioning method.Patients can be lifted by staff on the sheet on which they lie whilst one individual turns the head. This requires at least 5 members of staff and is exceptionally demanding from a manual handling perspective, particularly if patients are obese.

Repositioning patients is a physically demanding and time-consuming task for ICU staff, but it is vital for patient care. The high workload involved places a significant strain on staff capacity and contributes to several risks:i.At least 5 staff are required to reposition the patient every 2–4 h. This mandates drawing staff from across the ICU and leads to nurses having to leave other patients to support the repositioning exercise. This results in recurrent interruptions in care for other patients who are critically dependent on the drugs or machines which the nurses oversee. This practice necessitates breaches of national standards on nurse:patient ratios and jeopardises the lives of other patients.ii.Any adverse event of an unsupervised patient on ICU would be all but impossible to defend medico-legally; liberating nurses to care for their own patients is therefore vital.iii.Staff shortages on ICU in the post-pandemic era may be more significant than they were pre-pandemic, exacerbating the challenges of liberating staff to perform repositioning.iv.The process of repositioning is currently far from risk free. As sedated, ventilated patients are moved about the bed, there is a risk of removal or displacement of lines or tubes on which the patient’s life is continually and critically dependent. This occurs in up to 12.5% of proned patients [3].v.Improper repositioning risks damage to organs such as the eyes, liver, pancreas, or genitals and exposes patients to pressure sores, which are the most common source of litigation of ICUs in the UK [5].vi.Recurrent repositioning is manually demanding for staff. Manual handling injuries cost the NHS £18bn in 2019/2020 [6], and any device which reduces this risk will ease staffing problems and the fiscal burden on the NHS as a whole.vii.Staff burnout remains an ongoing challenge on ICU [7], deepening the staffing crisis. A device which unburdens staff will reduce burnout and staffing challenges.

This has led to the development of the inflatable prone repositioning device (IPRD) known as the ‘BathMat’ that is intended to improve the safety and ease of repositioning patients whilst reducing the number of staff and the time required. The BathMat consists of a multi-vessel inflatable pillow, placed underneath a proned patient, which can be inflated to raise the patient’s chest and hips. With the patient raised, repositioning of the head and arms can occur with ease, before the device is deflated and the patient is returned to the resting position. The BathMat has four main benefits for patients and staff:Repositioning of the head and arms occurs without the risks described above.It reduces the number of staff required from 5 to 2.It reduces the time it takes for repositioning from 30–60 min to 10 min.It removes the majority of the manual handling workload.

This study is required to demonstrate the effectiveness of this device in the clinical setting and provide data regarding its safety, usability, and reliability.

## Study design, aims, and objectives

### Aim

To determine the change in total staff time required for repositioning proned patients using the BathMat and to assess the safety of use when compared with standard care.

### Objectives and outcomes

See Table 1.

**Table 1 Tab1:** Objectives and outcome measures

Objective	Outcome measure	Source
Primary objective To investigate the staff time required to perform a proned patient reposition exercise. This will include the total number of staff required as well as the duration of the exercise	a. Difference in number of staff required to reposition each patient b. Difference in time required to reposition each patient	The number of staff required to reposition the patient and the time required will be collected by clinical teams by scanning a quick response (QR) code unique to each patient every time a patient is repositioned
Secondary objectives a. Assessment of the number of repositioning exercises undertaken for each patient within a proning intervention b. The number of minor or major adverse incidents associated with repositioning patients whilst in the prone position. This includes events such as line or tube displacement c. The manual handling requirement to reposition d. In patients who suffered a major or minor adverse event (as defined in secondary outcome b), assessment of the healthcare costs relating to that event at 3 months following ICU discharge	a. Number of documented repositioning exercises b. Adverse events documented c. Difference in Likert scale measure of difficulty of repositioning between control and intervention groups d. Healthcare costs of adverse event at 3 months post discharge	a. Clinician form entry from QR code (as above) b. Clinician form entry from QR code (as above), research team form entry c. Clinician form entry (from QR code as above) d. Research team form entry

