## Training in use of device

All staff expected to be involved in repositioning will receive training in the use of the device in line with the instructions for use. This may be delivered by local or central study staff. Clinical staff will be responsible for the appropriate use of the device. Before using the device clinically, they may refresh training using a centrally produced training video or reviewing the training materials as required to ensure adherence to the instructions for use, which are also kept with the device controller at all times, with a quick reference guide should this be required by clinical staff.

Any staff receiving training in the use of the device will also receive training in the data entry requirements for assessing the primary outcome and other data only able to be recorded contemporaneously by clinical staff detailed in Tables 2 and 3. Any clinical staff using the device is required to have this training in order to use the device.

**Table 2 Tab2:** Data to be entered by clinical team after each repositioning exercise

Repositioning start time Repositioning ready time Repositioning stop time Number of staff taken to reposition Cause for any delays in repositioning Complications during repositioning Perceived ease of repositioning Perceived acceptance of use of BathMat (if used) Other comments, reasons for delay in repositioning, etc.

**Table 3 Tab3:** Repositioning complication domains

Tracheal tube blockage/displacement/extubation Infusion line kink/displacement Nasogastric tube displacement Bleeding from airway Other repositioning complication	

A training log will be kept by local site teams detailing staff trained and will be monitored centrally. Recruitment at each site will not begin until an adequate proportion of local clinical staff has received this training in order to ensure safe use of the device and appropriate data entry by clinical staff.

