### Placement of inflatable device

When a proned patient is due to be repositioned using the BathMat, the device will be placed underneath the patient and underneath their sheet either before or after they are proned, but before any repositioning exercise is planned. Participants will be turned prone in accordance with local ICU protocols. The placement of the BathMat will be checked to ensure the shoulder line on the BathMat aligns with the upper edge of the patient’s shoulders, the inflatable device has not wrinkled underneath the patient, and that the device and patient are positioned correctly on the bed. Ultimately, the final position of the patient on the mat must be decided by the clinical team, taking into account the size and shape of the patient but also the size and range of movement of the neck.

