### Removal of device from patient

Once the proning session is completed, the patient will be returned supine as per standard ICU protocol. The inflatable device can be removed immediately before or after returning supine. First, the inflatable device is disconnected from the control unit by squeezing the clasps of the non-interchangeable connector and pulling the two halves apart. The patient can then be rolled to enable the device to be removed.

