### Data entry by clinical team

When enrolled patients require repositioning, the total staff time taken to reposition must be recorded—this is the primary outcome measure. An online clinical data entry Microsoft form, accessible via QR code or hyperlink at the patient’s bedside using any device, will allow staff to submit data from Table 2. Table 3 details domains for repositioning complication. The live Microsoft form will collect patient data linked to the participant’s study number and be managed by the central study team. It will not contain any other identifiable information.

This requires the bedside nurse primarily responsible for patient care to record the time (HH:MM 24-h clock format) at each point of repositioning as stated below, and the number of staff required to do so, by scanning the ‘repositioning QR code for bedside nurse’ unique to that patient or using the appropriate unique uniform resource locator (URL). Time should be rounded to the nearest minute, without the use of decimal places or seconds. The form must be completed after each repositioning manoeuvre and does not require any timing calculations by clinical staff. Instead, the form asks for four data points from the bedside nurse regarding the primary outcome:Repositioning start time: The time when the first staff member required to reposition the patient (in addition to the bedside nurse) enters the bed space to begin repositioning.Repositioning ready time: The time when the last member of staff required to reposition the patient has arrived in the patient’s room or bedspace.Repositioning stop time: The time when the last member of staff who was drawn in to assist the bedside nurse with repositioning has left the patients room or bedspace.The number of staff taken to reposition: Includes all staff (including the bedside nurse) who have helped in the repositioning manoeuvre. This does not include anyone outside of the patient’s room or bedspace who was available for help, and not actively involved in the repositioning manoeuvre.

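### Secondary outcome b counts incidents at repositioning, and nothing in the protocol assigns incidents at mat placement or removal, which happen only in BathMat sessions, to the comparison

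*Protocol article*

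**What the plan says.** All references are to the protocol article.

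- **Scope of the outcome.** In Objectives and outcomes (Table 1), secondary objective b is "The number of minor or major adverse incidents associated with repositioning patients whilst in the prone position", with the addition "This includes events such as line or tube displacement". Background and rationale uses repositioning as a defined term for turning the head and moving the arms of a patient who is already prone.
- **Sources.** Table 1 lists them as "b. Clinician form entry from QR code (as above), research team form entry".
- **Trigger for the bedside form.** Table 2 is titled "Data to be entered by clinical team after each repositioning exercise" and its safety item is "Complications during repositioning". Data entry by clinical team adds: "The form must be completed after each repositioning manoeuvre". Table 3, the only list that names tube, infusion-line and nasogastric displacement, is headed as a list of repositioning complications.
- **Placement.** Under Placement of inflatable device, "the device will be placed underneath the patient and underneath their sheet either before or after they are proned", and ahead of any planned repositioning.
- **Removal.** Removal of device from patient allows this just before or just after the return to supine, and says "The patient can then be rolled to enable the device to be removed".
- **Aim.** The Aim section includes assessing how safe the device is in use relative to standard care.
- **Costs.** Outcome d covers the healthcare costs of events as outcome b defines them.

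**The concern.** Placement and removal belong to one method only. A standard-care session has the turn to prone, the repositionings and the return to supine. A BathMat session has all of these plus the mat going in and coming out. Outcome b looks at the manoeuvre the device is meant to make safer and, as worded, does not take in the handling that the device adds. An infusion line pulled while the patient is rolled to free the mat is an incident of using the device. It is not an incident of repositioning, and if the patient is already supine it does not occur whilst prone either.

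If such events stay outside the count, the between-method summary understates incidents in BathMat sessions and has no matching omission in standard-care sessions. The same events also drop out of the outcome d costs. The Statistical analysis section says the study's findings on safety and performance will support design refinement, performance claims and regulatory planning, so a one-sided count would carry forward even though it is not formally tested.

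**Working it through.** The protocol states no figure on this point, so there is nothing to reproduce. The check has two parts: reading the texts together, and sizing the gap under stated assumptions.

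**1. Which handling steps does outcome b reach?**

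| Step | BathMat session | Standard-care session | Within outcome b as worded? | Bedside form triggered in the text? |
|---|---|---|---|---|
| Turn to prone | yes | yes | no | no |
| Mat placement | yes | no | no | no |
| Repositioning (head and arms) | yes | yes | yes | yes |
| Return to supine | yes | yes | no | no |
| Mat removal, with possible roll | yes | no | no | no |

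The two turns are left out in both arms, so that omission is balanced. The two mat steps are left out in one arm only.

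**2. Can placement be a separate step?** Yes. Decision to prone and randomisation describes the mat going in during the proning process, but also allows randomisation after the patient has been proned. A patient then allocated to BathMat for that session needs the mat put under them while prone, which the placement section permits.

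**3. Handling occasions (upper illustration only).** The Sample size section assumes 2, 3 or 4 repositionings per session with proportions 1/5, 3/10 and 1/2.

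- Mean repositionings = 2 × 0.2 + 3 × 0.3 + 4 × 0.5 = 3.3.
- Placement and removal both separate: 2 / (3.3 + 2) = 38% of mat-related handling occasions lie outside outcome b (2/4 = 50% at 2 repositionings, 2/6 = 33% at 4).
- Only removal separate: 1 / (3.3 + 1) = 23% (1/3 = 33% at 2, 1/5 = 20% at 4).
- Both absorbed into the prone and supine turns: close to none.

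The denominators leave out the two turns. The figures count occasions, not risk.

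**4. Possible effect on a ratio (assumed risks).** Suppose BathMat halves the incident risk per repositioning, so the counted per-session ratio is 0.50. Let each mat step carry k times the risk of one standard-care repositioning. With both steps separate, the ratio including them is (0.5 × 3.3 + 2k) / 3.3:

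- k = 0: 1.65 / 3.3 = 0.50
- k = 0.5: 2.65 / 3.3 = 0.80
- k = 1: 3.65 / 3.3 = 1.11

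The halving and every value of k are assumptions. The calculation shows direction: adding the omitted events can raise the BathMat count or leave it unchanged, but cannot lower it.

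**The case against.** The strongest reply is that these events are probably recorded somewhere.

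- Outcome b has a second source, the research team form.
- The Safety section has the research team record the items in Tables 3 and 5 daily. That recording is not tied to a repositioning, and Table 3 includes line and tube displacement.
- Table 5 covers ease of introducing the mat, manual handling concerns and free comments, and Table 6 has an 'Other' item.
- Adverse events and device deficiencies go to the site principal investigator, and staff can report device concerns to the central team.

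This stands as far as documentation goes. A reader might infer that a displacement at mat removal would go unrecorded; the text does not support that. Nor does it support the inference that the Safety section bars non-serious displacements. Its limit to serious, trial-related events applies to unexpected events, and displacement is a prespecified domain.

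Documentation is not the same as being counted, however. No text places an incident at placement or removal in outcome b or in a comparison of methods. Table 3 is headed for repositioning, while Table 5 has no removal item and is collected only where staff who used the device are available.

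Three further points have weight. Both mat steps may be absorbed into turns common to both arms. Outcome b is descriptive and the trial is not powered for it. Incidents at repositioning are also a matched exposure and worth reporting in their own right. These points limit the size and consequence of the gap; they do not make it two-sided.

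**Conclusion.** The point holds as one of outcome scope. As worded, outcome b and its bedside form count incidents at repositioning whilst prone. Incidents at mat placement or removal are not assigned to outcome b, to a comparison between methods, or to the outcome d costs. Because those steps exist only in BathMat sessions, the omission can only favour the device.

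The size is unknown. The protocol gives no incident risk for placement or removal. Its figure of up to 12.5% for displacement of lines or tubes is quoted for proned patients in the context of current repositioning, so it cannot be applied to the mat steps. The 38% is an upper illustration of handling occasions at 3.3 repositionings per session with both steps separate; a reader might take it as the share of incidents missed, which it is not. Nor do the documents show that the comparison would reverse, since the ratio of 1.11 depends on assumed risks. If both steps are done within the prone and supine turns, the gap is small.

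This is a worthwhile, low-cost correction to a descriptive outcome. It does not touch the primary endpoint.

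**What to change.** 1. In Table 1, define the outcome b window in both arms as the whole proning session: from the turn to prone, with any mat placement, to the return to supine, with any mat removal. State that removal after the return to supine is included.
2. Add one end-of-session entry to the existing QR form, carrying the Table 3 domains for the turns, placement and removal, and completed in BathMat and standard-care sessions alike.
3. Report incidents at repositioning, and incidents at placement, turning or removal, separately and combined by method. Outcome d then follows the widened definition.

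The cost is one short extra entry per session and a wording change. The combined count will include events from turns common to both arms, which adds some noise; the separate reporting keeps the repositioning comparison visible.
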